### Participant timeline {13}

#### Follow-up study visits

Irrespective of the randomized group, both Index and Partner participants individually will complete in-person questionnaires administered by study staff on interpersonal factors and partner involvement, outcomes, and illicit drug use and service usage at 1-week (visit 2), 1-month (visit 3), 4-month (visit 4), and 7-month (visit 5). In both study arms, Index participants are provided with $50 cash reimbursements after each completed visit. If the Partner attends and completes the study visits with Index participants, each will receive a $55 cash reimbursement after each completed visit.

### Sample size {14}

The primary superiority hypothesis for this trial, that those randomized to the intervention will have a higher 6-month probability of treatment initiation compared to those in the control group, was powered based on our previous work and comparable results of community-based RCT studies with PWID that suggest a HCV treatment initiation rate of 30% for those in the intervention group (13% in control group), and a retention rate of 80% (based on our previous cohort of injecting partnerships) [37, 38]. We will have 80% power to detect this effect with a sample size of 250, corresponding to a risk ratio of 2.0, at the 5% significance level.

### Recruitment {15}

Participants will be recruited through referrals (e.g., phone calls and in-person study handouts to clients) from CBOs and clinics providing HCV testing. Study staff will also perform street outreach, passing out study handouts to interested people around San Francisco venues where PWID frequent.

## Assignment of interventions: allocation

### Sequence generation {16a}

The sequence of random assignments will be generated and uploaded into REDCap for use with enrollment. A simple randomization allocation table will be generated using sorted random values to distribute allocation to the intervention or control arm. This will allow for concealment allocation as research staff will not be able to anticipate allocation.

### Concealment mechanism {16b}

Group assignment of participants is carried out by a random assignment tool within REDCap. The randomization allocation table and settings will only be accessed by the data manager.

### Implementation {16c}

Participants will be enrolled by the study staff at primary study sites. The assignment of participants to either the intervention or control arm will be done electronically through REDCap at the time of randomization. Participants cannot be reassigned to different arms.

### Assignment of interventions: blinding

#### Who will be blinded {17a}

Due to the nature of the study design, the delivery of the intervention will not be blinded. The result of the concealment of a new step in the allocation sequence will be disclosed to participants and staff. Those involved in the data analyses will be blinded to the group allocation. All analyses will be performed by the study’s biostatistician, select study staff under the guidance of the study’s biostatistician, and the principal investigators (PIs) while blinded to study allocation.

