#### Procedure for unblinding if needed {17b}

The study participants and study staff interacting with participants will not be blinded. Analytic datasets will be blinded to allocation. Unblinding will occur only after all statistical analyses are completed and the primary outcomes have been fully analyzed and documented.

Unblinding of a participant’s allocated intervention will be permissible under the following circumstances: (1) medical emergency: if a participant experiences a serious adverse event or medical emergency where knowledge of the intervention is necessary for providing appropriate medical care, or (2) regulatory request: if requested by regulatory authorities for safety monitoring or audit purposes.

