#### Confidentiality {27}

All collected information will be kept strictly confidential and stored in accordance with national regulatory approvals. The PIs and biostatistician will be the only study personnel with access to the code list.

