### Oversight and monitoring

#### Composition of the coordinating center and trial steering committee {5d}

While this study does not include a formal Trial Steering Committee (TSC), oversight is ensured through regular meetings and structured processes involving the following groups:

Principal Investigator and Research Team: The PI and core team (clinical research coordinators, graduate student researchers, and data manager) provide day-to-day support. Responsibilities include participant recruitment, obtaining informed consent, intervention delivery, and data collection. The team also supports protocol development, study design and conduct, and manuscript preparation with guidance from the investigators. The team meets twice weekly with the PI to discuss trial operations and every 1–2 months to review progress, publications, and adherence to the protocol.

Community Academic Board (CAB): The CAB serves as the Stakeholder and Public Involvement Group (SPIG), composed of community representatives, patient advocates, and academic members. This board meets 6–12 times per year in person to provide input on recruitment strategies, community engagement, and dissemination plans.

Institutional Review Board (IRB): The IRB reviews the trial annually or as needed for protocol amendments, ensuring compliance with ethical and regulatory standards.

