#### Frequency and plans for auditing trial conduct {23}

Trial conduct is monitored through internal audits conducted by the data manager on a weekly and monthly basis to ensure data quality, integrity, and adherence to the protocol. Findings are reported during biweekly operational meetings with the investigators and coordinating team. Issues occurring at the study site are reported immediately to the principal investigator and discussed during these regular meetings. Additionally, the principal investigator and coordinating team meet twice a year to specifically review the integrity of intervention delivery and adherence to the trial protocol.

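### The PIs and any core-team analysts are described as blinded, but their other listed duties mean a masked dataset gives them hidden arm labels rather than blinding

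*Protocol article*

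**What the plan says.** All of this is in the protocol article.

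- **Who analyses, and in what state.** Section {17a} gives the general rule: "Those involved in the data analyses will be blinded to the group allocation". It then names the biostatistician, select study staff under that person's guidance, "and the principal investigators (PIs) while blinded to study allocation". Sections {18a} and {19} repeat that analysis is done blinded, and mention team members and collaborators.
- **How the blinding works.** Section {17b} gives the mechanism: "Analytic datasets will be blinded to allocation".
- **Who knows allocation.** Section {17a} says that each allocation "will be disclosed to participants and staff". Section {17b} says: "The study participants and study staff interacting with participants will not be blinded".
- **What the PI and core team do.** Section {5d} describes the PI with the coordinators, graduate student researchers and data manager: "Responsibilities include participant recruitment, obtaining informed consent, intervention delivery, and data collection". This team meets the PI twice weekly.
- **Review of delivery.** Section {23} states that "the principal investigator and coordinating team meet twice a year to specifically review the integrity of intervention delivery".
- **Access to lists.** Section {16b} restricts the allocation table to the data manager. Section {27} states: "The PIs and biostatistician will be the only study personnel with access to the code list". It does not say what that list links.

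**The concern.** The trial is open to participants and staff, so blinded analysis is a safeguard that readers of the results will rely on. It is meant to ensure that judgements made during analysis are not influenced by knowing which arm gains. The article gives some of the same roles two states that do not fit together: blinded as analysts, and informed as people who run, deliver or review the intervention.

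If the staffing stays as described, analytic decisions could be made or guided by people who can tell the arms apart, and the trial report would claim a protection that those people did not have. This applies to whatever judgement remains at the analysis stage. Section {20a} defers a detailed plan to a later document, and the deferral itself is not criticised here.

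**Working it through.** No arithmetic applies. The check sets the statements side by side for each analyst group named in {17a}.

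**1. The PIs.**
- Stated as analyst: blinded ({17a}).
- Stated elsewhere: the PI heads the group whose duties include intervention delivery and data collection ({5d}), meets that group twice weekly on trial operations ({5d}), is told at once of problems at the site, and reviews the integrity of delivery twice a year ({23}).
- Result: the two descriptions conflict for the PI who holds these duties. Sections {5d} and {23} speak of one PI and {17a} of several, so for any further PI the conflict depends on whether that person shares the duties.

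**2. Select study staff.**
- Stated as analysts: blinded ({17a}).
- Stated elsewhere: allocation is disclosed to staff without qualification ({17a}), while {17b} confines the unblinded group to staff in contact with participants.
- Result: on the wording of {17a}, staff are both told the allocation and blinded to it. On the narrower wording of {17b}, the conflict arises only if the selected analysts have participant contact. The data manager belongs to the core team and holds the allocation table ({5d}, {16b}), and nothing in the article excludes that role from analysis.

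**3. The biostatistician.**
- Stated as analyst: blinded ({17a}).
- Stated elsewhere: access to the code list ({27}). No section gives this role participant contact, delivery duties or the allocation table.
- Result: no contradiction. One question remains. Section {19} describes a separate file linking identities to study IDs. If that is the code list, it does not itself show the arm. If the list decodes the arms, it would unblind its holder.

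**4. Does the masked dataset resolve groups 1 and 2?** Masking the arm variable works for someone who has no other route to allocation. Two routes may be open here:
- *Knowledge of individuals.* Only the intervention arm has the two counselling sessions ({11a}). Someone who knows that a few given people attended, and who can trace their records, can tell which coded arm is which. The PIs have the code list, so if it links identities to IDs they can trace records.
- *Content of the data.* Follow-up questionnaires ask about experience with the intervention (data sources, under {18a}). If such items stay in the analytic dataset, they can reveal the arm. The article does not say whether they are removed.

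For the PI and for any core-team analyst, the dataset therefore provides masked labelling. It does not provide the state that {17a} claims.

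**The case against.** The strongest reply has four parts.

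- **A mechanism is stated.** Section {17b} provides masked analytic datasets, and masked labels can be useful even to someone who knows some allocations. This stands against any claim that the trial has no blinded analysis. A reader might infer that the stated blinding does not exist at all. The article does not support that, because the mechanism is there and nothing contradicts it for the biostatistician.
- **The PIs may only guide.** In {18a}, {19} and {20a} the PIs can be read as giving guidance, and the sentence in {17a} can be read the same way. This is fair, and the article does not establish that every PI runs analyses. It does not remove the conflict, because {17a} attaches blinding to everyone involved in the analyses, and guiding them is involvement.
- **Duties are listed for a group.** Section {5d} does not say that the PI leads sessions, and {11a} assigns sessions to trained, certified staff members. The review in {23} is not said to show allocation participant by participant. This stands as a limit: the article shows roles that give access to allocation, not that a particular PI knows particular allocations.
- **The staff analysts are unidentified.** It would be an assumption to say that the selected analysts deliver sessions. This also stands, so for them the point is conditional.

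It might also be inferred that the code list compromises the biostatistician. The list is undefined, and an identity list alone does not disclose arm to someone without participant contact.

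**Conclusion.** The point holds in limited form. For the PI, and for any analyst drawn from the core team, the blinding stated in {17a} is contradicted by duties stated elsewhere, and the masked dataset does not restore it. For the biostatistician it is not contradicted, subject to a definition of the code list. For select staff with no participant contact, it depends on which of the two statements about staff in {17a} and {17b} applies.

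The size cannot be expressed as a change in an estimate or in power. In scope, the claim of blinded analysis covers all analyses, primary and secondary. Of the three analyst groups named, one is in conflict (the PIs, at least the one leading the team), one is conditionally in conflict (select staff), and one is not.

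The conclusion assumes that the duties in {5d} and {23} give their holders knowledge of at least some allocations. That is the natural reading for an open trial with twice-weekly operational meetings, but it is not stated outright. The point is more than missing detail, because the article affirms a safeguard that its own staffing does not deliver for some of those named.

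**What to change.** Reconcile {17a}, {17b}, {18a}, {19}, {27} and {5d} as follows.

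1. Limit the blinding claim to analysts with no intervention-delivery or participant-contact role, for example the biostatistician.
2. Have those analysts run and lock the primary and secondary analyses on coded arms. Remove intervention-only items (session attendance, experience with the intervention) from the dataset, and give these analysts no list that reveals identity or arm.
3. State that the PIs and core team are not blinded, and that they take part in analysis only after the primary results are locked. Align the rule in {17b} on when unblinding occurs with this.
4. Define the code list in {27}: what it links, and who holds it before the lock.
5. Settle whether allocation is disclosed to all staff or only to those in contact with participants.

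The cost is revised wording and one stripped dataset, which the data manager could prepare because that role already holds the allocation table. The downside is that the PIs and core team must wait for the lock. The article does not show whether the biostatistician can carry the locked analyses alone. If not, another analyst without participant contact would serve. Recruitment is expected to run to December 2027, so there is time to make the change before the final analysis.

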#### Procedure for unblinding if needed {17b}

The study participants and study staff interacting with participants will not be blinded. Analytic datasets will be blinded to allocation. Unblinding will occur only after all statistical analyses are completed and the primary outcomes have been fully analyzed and documented.

Unblinding of a participant’s allocated intervention will be permissible under the following circumstances: (1) medical emergency: if a participant experiences a serious adverse event or medical emergency where knowledge of the intervention is necessary for providing appropriate medical care, or (2) regulatory request: if requested by regulatory authorities for safety monitoring or audit purposes.

### Data collection and management

#### Plans for assessment and collection of outcomes {18a}

Following randomization, participants will complete detailed questionnaires at enrollment, 1 week, 1 month, 4 months, and 7 months. All analyses will be performed by the study’s biostatistician as well as by study team members and collaborators under the guidance of the study’s biostatistician and the PIs while blinded to study allocation.

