### Objectives {7}

The primary objective of the study is to estimate the proportion of people newly diagnosed with chronic HCV infection who start direct-acting antiviral (DAA) treatment and the time from enrolment to starting DAA treatment by a randomized group.

H1a: Those randomized to the intervention will have a higher 6-month probability of treatment initiation compared to those in the control group.

H1b: Those randomized to the intervention will have a significantly shorter time to HCV treatment initiation compared to those in the control group.

Secondary objectives are:To measure changes in injecting-related interpersonal factors and partner support factors at 1-week, 1-month, 4-month, and 7-month post-randomization by randomized group.To determine between-group differences in HCV DAA treatment completion and sustained virologic response at 12 weeks post-treatment completion.

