#### Trial design {8}

The *Y*ou’re *E*mpowered for *T*reatment *I*nitiation (YETI) Partner study is a non-blinded, parallel-group, two-arm, superiority randomized controlled trial with 1:1 allocation ratio to assess the efficacy of a two-session dyadic intervention to involve injecting partners as peer navigators to HCV treatment.

We aim to recruit and randomly allocate 250 persons living with HCV (“Index participants”) and their primary injecting partners (“Partner participants”) to either a control or intervention group. The primary endpoint is starting HCV treatment; secondary endpoints are treatment completion and sustained virologic response at 12 weeks post-treatment completion (sustained virologic response 12 weeks post-treatment, SVR-12). A description of the overall study design is in Fig. 1 and the schedule of enrollment, interventions, and assessments is in Fig. 2. Eligible PWID with evidence of HCV infection who enroll will be randomized (1:1) to either a control or intervention group. Both Index and Partner participants will participate in all five study visits: baseline (visit 1), 1-week (visit 2), 1-month (visit 3), 4-month (visit 4), and 7-month (visit 5). Questionnaires will be administered to the Index and Partner at all five visits. Intervention session 1 will be administered with the Index participant only at visit 1, and intervention session 2 with both the Index and Partner participants at visit 2. To expand our ability to capture primary endpoint data, participant data will be linked to their electronic health record (EHR) for HCV treatment start date, completion date, and SVR-12. The study protocol (version 1.4, 03/21/2024) follows the Standard Protocol Items: Recommendations for Interventional Trials (SPIRIT) Statement. The trial has been registered at ClinicalTrials.gov (ID: NCT06179498).

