### Who will take informed consent? {26a}

#### Written consent to participate

Eligible participants (Index and Partner) who present in-person at the study site for visit 1 will individually undergo a fully informed written e-consent protocol led by trained study staff. Research participants should be able to understand, as completely as possible, what procedures, risks, benefits, alternatives, and rights are involved, and make an informed choice about being in the study without pressure or undue inducement to participate.

During this process, consent will be requested for (a) study participation and (b) the release of medical records for up to 5 years post-participation. To help protect our participants’ privacy, we have received a Certificate of Confidentiality from the National Institute of Health. Our consent form and plain language companion document, approved by the IRB at our university, were developed in partnership with members of our community-academic partnership through a series of group discussions focused on improving readability and transparency. Directly after voluntary consent is obtained and documented on REDCap, participants will begin visit 1. REDCap (Research Electronic Data Capture) is a secure, web-based software platform designed to support data capture for research studies, providing (1) an intuitive interface for validated data capture; (2) audit trails for tracking data manipulation and export procedures; (3) automated export procedures for seamless data downloads to common statistical packages; and (4) procedures for data integration and interoperability with external sources [35, 36]. Study data were collected and managed using REDCap electronic data capture tools. Those who decline study enrollment will receive information about HCV prevention strategies and HCV treatment resources and will be paid $5 for their time.

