#### Data sources

The YETI Partner Study will use a combination of EHR and questionnaires to collect data.

EHR data will include HCV testing, treatment initiation, completion, and cure information, which is requested every 3 months for Index participants via medical record number (MRN).

Self-report data will be collected individually through staff-administered questionnaires at the baseline screening visit, after informed consent, and all subsequent visits.Data will be collected individually and in separate rooms for the Index and Partner participants to ensure accurate responses. Questionnaires will assess the following domains:Demographic characteristics will include age, gender, sexual orientation, race/ethnicity, education level, employment status, sources of income, food security using the USDA Household Food Security Survey Model, and living arrangements.Healthcare access characteristics will include access to providers, emergency care, and barriers to access.HCV knowledge will be measured using an adapted HCV Knowledge questionnaire from the Canada Treatment Information Exchange (CATIE).Drug use questions will cover methods, frequency, and substances used, equipment sharing and harm reduction practices, attitudes towards current use, receipt of opioid substitution therapy, overdose, and alcohol and tobacco use. These measurements have been adapted from questions employed by the PIs.Partner and relationship characteristics will be measured using information about partner dynamics, social networks, injecting dynamics, and partner support via the 54-item IDIP scale [32], the Source-Specific SPS-24 [39], and the SPS-24 adapted for HCV treatment initiation.Police interactions will include interactions with police and history of incarceration or parole.General health includes HCV history, quality of life, and depression. Depression will be measured using the standardized Center for Epidemiologic Studies Depression Scale (CESD) [40].Stigma and racism will be captured using the Substance Use Stigma Mechanisms Scale (SU-SMS) [41] with adaptations and the Experiences of Discrimination scale with minor adaptations in language [42].

Subsequent visits will include questions related to the Index’s and Partner’s experiences with the intervention and self-reported outcome data.

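### As worded, the enrolment questionnaire follows unblinded randomization, so the baseline partner-support scores behind the change-by-arm comparison can be influenced by the assigned arm

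*Protocol article*

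**What the plan says.** All places are in the Protocol article.

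- Section {18a}, on how outcomes are assessed and collected, reads: "Following randomization, participants will complete detailed questionnaires at enrollment, 1 week, 1 month, 4 months, and 7 months". The enrolment questionnaire is listed among those that come after randomization.
- Data sources: "Self-report data will be collected individually through staff-administered questionnaires at the baseline screening visit, after informed consent, and all subsequent visits". The instruments include the 54-item IDIP, the SPS-24 and an SPS-24 adapted to HCV treatment initiation.
- Written consent to participate: "Directly after voluntary consent is obtained and documented on REDCap, participants will begin visit 1".
- Trial design {8}: "Eligible PWID with evidence of HCV infection who enroll will be randomized (1:1) to either a control or intervention group", and "Intervention session 1 will be administered with the Index participant only at visit 1".
- Who will be blinded {17a}: the result of each allocation step "will be disclosed to participants and staff". Procedure for unblinding {17b} confirms: "The study participants and study staff interacting with participants will not be blinded".
- Objectives {7}, first secondary objective: "To measure changes in injecting-related interpersonal factors and partner support factors at 1-week, 1-month, 4-month, and 7-month post-randomization by randomized group".
- Statistical methods {20a}: an exploratory linear mixed model relates changes in these scores, over time and by group, to treatment initiation. The mixed models are then extended to actor and partner effects.

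**The concern.** A baseline protects a randomized comparison only if the arm cannot have influenced it. Here the one questionnaire before the 1-week visit is described as coming after randomization. By then the respondent and the interviewer may both know the arm, and on the wording the questionnaire could even follow session 1. That session asks the Index participant about past support from the partner and how the partner could help with starting treatment, which is close to what the IDIP and SPS-24 scales measure.

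An Index participant who has just learned of assignment to a partner-support intervention may rate that support differently from one assigned to the handout alone. The arms would then differ at baseline for a reason other than chance. A change from that baseline, or a model adjusted for it, would no longer estimate the effect of the intervention on partner support. Blinding the analysts does not help, because the distortion is already in the data.

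**Working it through.** **Order of events.** No design figure is at issue, so the first check sets the sections side by side.

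1. {18a} puts the enrolment questionnaire after randomization.
2. Data sources fixes it only relative to consent. Calling the visit a baseline screening visit hints at an earlier position but does not give the order against randomization.
3. Trial design {8} puts enrolment before randomization. It does not say where the questionnaire falls.
4. The consent section starts visit 1 directly after consent and describes no separate visit before randomization.
5. Session 1 is at visit 1. Its order relative to the questionnaire is not given in the text.

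So one sentence states an order, and no visible section replaces it with another.

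**Which analyses use the exposed scores.**

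- Exposed: the secondary objective on change by arm, the mechanism model, and the actor-partner models. The article does not say outright that change is measured from enrolment, but no other questionnaire precedes the 1-week visit.
- Slightly exposed: the adjusted analyses in {20b}, which name healthcare access and injecting network size. These are self-reported but largely factual.
- Not materially exposed: the unadjusted primary comparison of treatment initiation, which uses no baseline score; and the subgroups by age, gender, race and ethnicity, which learning the arm would hardly move.

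**Direction and scale.** The document gives no figure for how far disclosure moves a score, so the following is illustration only. Assume a true follow-up effect of 0.3 SD, a baseline shift of b SD in the intervention arm only, and a baseline-to-follow-up slope of 0.5 or 0.7.

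- Change contrast = 0.3 − b
- Baseline-adjusted contrast = 0.3 − slope × b

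| b (assumed, SD) | Change contrast | Adjusted, slope 0.5 | Adjusted, slope 0.7 |
|---|---|---|---|
| +0.1 | 0.20 | 0.25 | 0.23 |
| +0.2 | 0.10 | 0.20 | 0.16 |
| +0.3 | 0.00 | 0.15 | 0.09 |
| −0.1 | 0.40 | 0.35 | 0.37 |
| −0.2 | 0.50 | 0.40 | 0.44 |
| −0.3 | 0.60 | 0.45 | 0.51 |

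An upward shift at baseline hides part of a real effect, and a downward shift inflates it. Which column applies depends on whether the enrolment score enters the mixed model as an outcome or as a covariate, which the article does not state.

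**The case against.** The strongest reply is that {18a} is a one-line summary in which a single opening phrase covers five time points, and that it was not meant literally for the first. Trial design {8} has people enrol and then be randomized, and Data sources speaks of a screening visit, which ordinarily precedes allocation. The schedule in Fig. 2 is not available here, and the article condenses a full protocol (version 1.4) where the order within a visit would normally be set out.

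Much of this stands. A reader might infer that baselines in this trial are in fact being collected after disclosure. The document does not establish that; it shows only that the published sentence says so and that nothing visible corrects it. Nor can the article be faulted for leaving out a detailed visit 1 sequence. The point rests on the order that it does state.

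A reader might also infer that the primary result, or every adjusted and subgroup analysis, is compromised. The text does not support this. The primary comparison uses treatment start dates by arm, the trigger for the imbalance adjustment in {20a} is demographic variables, and HCV knowledge and stigma are not named as covariates.

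What the reply does not remove is the need to act. If practice already takes the baseline first, the sentence is wrong and should be corrected. If practice follows the sentence, the secondary and exploratory analyses of partner support are exposed.

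**Conclusion.** The point holds in a limited form. As worded, {18a} places the enrolment questionnaire after an allocation known to respondent and interviewer, at the visit that also holds session 1. If that is followed, the baseline IDIP and SPS-24 scores are open to influence by the arm. The secondary change-by-arm comparison and the exploratory mechanism and actor-partner models would then be biased, in a direction that cannot be predicted and by an amount that cannot be estimated from the document.

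The tabulated values show how a shift would carry through; they are not a forecast. It would also go too far to say that the effect on partner support will be understated, since a shift the other way overstates it.

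The conclusion assumes that change is measured from the enrolment questionnaire, and that neither Fig. 2 nor the full protocol sets a different order.

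**What to change.** Reconcile Trial design {8}, {18a} and Data sources by stating one order for visit 1: consent, baseline questionnaire, REDCap randomization and disclosure, then session 1. Reword {18a} so that only the 1-week and later questionnaires follow randomization. Set REDCap to release the allocation only once the Index baseline form is marked complete.

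A Partner may not attend with the Index, so some Partner baselines could still come after disclosure. Flag any Index or Partner baseline taken after disclosure and run a sensitivity analysis on it. Do not exclude these records from the main analysis: that would be a post-randomization exclusion, could differ by arm, and would shrink the intact-dyad sample.

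Recruitment began in March 2024 and is expected to run to December 2027, so the change can still protect later enrolments. For people already enrolled, report the order actually used.

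The cost is a minor workflow constraint at visit 1 and one REDCap setting, with no extra visit or staff. If the baseline is already taken first, correcting the wording is enough.
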